### Sample size

The number of samples required for this study was calculated based on weight as a main dependent variable. The results of a previous study were used to calculate the sample size [47]. Sample size was calculated with α = 0.05 and power of 80% (1-β = 0.8). the sample size in each group was determined to be 20 patients; assuming a drop of 20%, 25 patients will be admitted to each group.

$$\begin{array}{c}\mathrm S1=2.8\\\mathrm S2\;=2.9\\\mathrm{Sp}\;=\;8.125\\\mathrm\mu1-\mathrm\mu2=2.5\\\end{array}$$

$$\begin{array}{c}\mathrm n=\frac{2\mathrm{Sp}^2\left({\mathrm Z}_{1-{\displaystyle\frac{\mathrm a}2}}+{\mathrm Z}_{1-\mathrm\beta}\;\right)^2}{\left(\mathrm\mu1-\mathrm\mu2\right)^2}\end{array}$$

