### Inclusion and exclusion criteria

For this study, 50 patients with weight regain and food addiction and with the following inclusion criteria will be included in the study: aged 18–50 years; BMI ≥ 25 kg/m2; willingness to participate in the study; not having diseases such as cancer, thyroid, renal or liver (except fatty liver); non-pregnant or lactating or menopause or professional athlete; not use of any antibiotics in the last three weeks and any protein or probiotic supplement in the last month.

Patients will be excluded if: taking any antibiotics during the study; using probiotic products (probiotic supplements, yogurt, cheese, cakes, biscuits, and probiotic pasta) or protein supplements during the study; using weight-loss or appetite-suppressing medications; pregnancy; consuming less than 90% of the supplements prescribed during the study Also, we will exclude participants who refuse to continue the study.

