### Study outcomes

The primary outcomes of this clinical trial are the changes in anthropometric indices (including weight, hip circumference, waist-to-hip ratio, fat mass, muscle mass) and food addiction score. Secondary outcomes are changes in eating behavior and serum levels of leptin, serotonin, and oxytocin.

If the patient has inclusion criteria, a consent form and personal information sheet will be completed for them.

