### Statistical analysis

In this study, data analysis will be performed by using SPSS version 21.0 (SPSS Inc, Chicago, Illinois) software. A paired t-test will be used to compare the mean of quantitative variables with normal distribution in each group between the beginning and the end of the study. The t-test will be used to compare the mean between the two groups at the beginning and end of the study. In the case of quantitative variables with non-normal distribution, Wilcoxon and Mann–Whitney tests are used, respectively. A repeated ANOVA test will be used for the variables measured three times during the study. Covariance analysis will be used to eliminate the effect of quantitative confounding factors. Quantitative confounding factors are physical activity and baseline values of the biochemical markers. A Chi-square test will be used to compare the qualitative variables between the two groups, and regression analysis will be used to eliminate the effect of qualitative confounding.

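### Weight outcomes are defined as changes, but the explicit between-group test compares means at single time points without the outcome's baseline, and the plan does not say which listed test decides

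*Protocol article*

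**What the plan says.** All references are to the protocol article.

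- **Sample size.** "The number of samples required for this study was calculated based on weight as a main dependent variable". The inputs are S1 = 2.8, S2 = 2.9, a printed Sp of 8.125 and a difference of 2.5, with two-sided α of 0.05 and 80% power. The result: "the sample size in each group was determined to be 20 patients; assuming a drop of 20%, 25 patients will be admitted to each group". The section does not say whether these figures are for change or for end values, and gives no unit.
- **Study outcomes.** "The primary outcomes of this clinical trial are the changes in anthropometric indices", with weight, hip circumference, waist-to-hip ratio, fat mass and muscle mass listed, together with the food addiction score. Body measurements are scheduled at baseline, week 6 and week 12.
- **Statistical analysis, between groups.** "The t-test will be used to compare the mean between the two groups at the beginning and end of the study". Mann–Whitney is the substitute for non-normal data. Change over time is tested by t-test only within each group (paired).
- **Statistical analysis, repeated measures.** "A repeated ANOVA test will be used for the variables measured three times during the study".
- **Statistical analysis, covariates.** Covariance analysis is planned for quantitative confounders: "Quantitative confounding factors are physical activity and baseline values of the biochemical markers".
- **Inclusion and exclusion criteria.** "aged 18–50 years; BMI ≥ 25 kg/m2", with no upper BMI limit. No SD of raw body weight appears anywhere.

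**The concern.** Three parts of the plan do not line up. The outcome is a change. The sample size works only with an SD that is credible for a change. The one explicit two-group t-test is applied to means at single time points, and no t-test of change between groups is stated. A within-group paired test does not estimate a treatment effect.

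In a population with BMI from 25 upward, differences in weight between people that exist before treatment would dominate a comparison of week-12 weights. A real 2.5 kg effect could easily be lost in them, and an arm that starts heavier by chance would look worse at the end for that reason alone. The usual protection is to adjust for the baseline of the outcome. The stated covariate list does this for the secondary hormone outcomes but names no baseline of weight, body composition, circumferences or food addiction score.

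At stake is whether the 80% power belongs to the analysis that will decide the trial, and whether two listed analyses of the same outcome could give different answers with no rule for choosing between them.

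**Working it through.** **1. The plan's own figure.** Pooled variance = (2.8² + 2.9²)/2 = 8.125, so the SD is √8.125 = 2.85. The printed Sp is therefore Sp². With z-values 1.96 and 0.8416:

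n = 2 × 8.125 × (1.96 + 0.8416)² / 2.5² = 20.4 per group.

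The stated 20 reproduces, rounded down. Power at 20 per group is 79.2% by the normal approximation and 77.1% by the noncentral t. Allowing for dropout, 20/0.8 = 25. Taking 8.125 literally as an SD would need 166 per group, so it was used as a variance.

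**2. What kind of SD is 2.85?** If it were the SD of raw weight, about 95% of patients would lie within 2 × 1.96 × 2.85 = 11 kg. At an illustrative height of 1.65 m, BMI 25 to 35 alone spans 68 to 95 kg, and the criteria set no upper limit. So 2.85 kg fits weight change and hardly fits raw weight.

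**3. If the week-12 t-test decides.** Inputs: 20 per group, difference 2.5 kg, two-sided α 0.05. The raw-weight SD is my assumption, shown as a range. SE of the difference = SD × √(2/20). Power is from the noncentral t with 38 df and noncentrality 2.5/SE.

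**4. If week-12 weight is adjusted for baseline weight.** Take 2.85 as the SD of change and equal raw SDs at both times. The implied correlation is ρ = 1 − 8.125/(2 SD²), which is 0.959, 0.982 and 0.990 for SD 10, 15 and 20. The residual SD is SD × √(1 − ρ²).

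| Assumed raw SD (kg) | SE of difference (kg) | Power, week-12 t-test | n per group for 80% | Residual SD after adjustment (kg) | Power, ANCOVA |
|---|---|---|---|---|---|
| 10 | 3.2 | 12.0% | 252 | 2.82 | 78.0% |
| 15 | 4.7 | 8.1% | 566 | 2.84 | 77.5% |
| 20 | 6.3 | 6.7% | 1,005 | 2.84 | 77.3% |

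Even an implausibly narrow raw SD of 5 kg gives the week-12 t-test only 34%. If all 25 per group completed, its power would be 13.9% (SD 10) to 7.2% (SD 20). The SE column is also the size of a typical chance difference between arms at baseline, and it exceeds the 2.5 kg target throughout.

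**5. If the repeated ANOVA decides.** Simulation of 4,000 trials per setting: 20 per group, three time points, SD of 12-week change 2.85, half the effect present at week 6, Greenhouse–Geisser correction.

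| Baseline SD (kg) | Group-by-time term | Group main effect |
|---|---|---|
| 12 | 76.5% | about 6% |
| 15 | 77.0% | about 6% |
| 20 | 77.1% | about 6% |

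The power of the same named procedure thus ranges from about 77% to about 6%, depending on the term that is read.

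**The case against.** The strongest objection is that weight is measured three times, so the plan assigns it a repeated ANOVA. The group-by-time term tests differential change with power near the planned 80%. On that reading the covariate list is coherent too: blood markers are taken only at the beginning and end, so they need baseline-adjusted ANCOVA, while three-time variables get their baseline through the repeated measures.

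Much of this stands. A reader might infer that the trial's real power is 7–12%, or that baseline is ignored for weight. The document supports neither as a flat statement. The low power follows only if the week-12 t-test decides, and its size rests on a raw-weight SD that the documents do not give. A reader might also say that 2.8 and 2.9 must be SDs of change. That is a strong inference from their size and the outcome definition, but the Sample size section does not say so and the cited source is not available here.

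The objection does not remove the problem. The Statistical analysis section names neither a group factor nor the group-by-time term, and does not say that the ANOVA takes precedence over the explicit t-test. Nor does the ANOVA clearly cover the food addiction score, also a primary outcome: the article describes that questionnaire for diagnosis and gives it no week-6 schedule.

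It can also be said that a journal article leaves the exact model to a full protocol or analysis plan. That excuses silence about a model term. It does not excuse a stated test on a different scale from the stated outcome, or a stated covariate list without the baselines of the primary outcomes.

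**Conclusion.** The point holds in conditional form. The explicit between-group test does not match the outcome definition or the apparent basis of the sample size, no primary-outcome baseline is a listed covariate, and the section does not fix which of its listed analyses decides for weight.

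Power for a 2.5 kg difference with 20 per group is about 12% to 7% if the week-12 t-test decides (assumed raw SD 10 to 20 kg), about 6% if the ANOVA's group main effect decides, and about 77% if its group-by-time term or an analysis of change decides. The last figure assumes that 2.85 is the SD of 12-week change; the ANOVA figures also assume half the effect at week 6. The claim that the planned power is lost outright is not supported. What is supported is that the 80% belongs to only some of the analyses the plan allows.

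**What to change.** - Name one primary between-group analysis of weight: ANCOVA of week-12 weight on arm with baseline weight as covariate, reporting the adjusted difference with its 95% CI. The group-by-time contrast at week 12 is an acceptable equivalent if it is named as such.
- Adjust every other continuous outcome, including body composition, circumferences and food addiction score, for its own baseline.
- State that the unadjusted week-12 t-test and Mann–Whitney are descriptive and do not carry the treatment conclusion.
- In Sample size, state whether 2.8, 2.9 and 2.5 refer to 12-week change and in what unit, and relabel 8.125 as Sp². If they do refer to change, power at 20 per group is about 77–79%.

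The cost is wording. Baseline weight and body measurements are already collected and the article reports the trial as still enrolling, so no patients or visits are added.

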### Randomization

This study is a triple-blind randomized controlled clinical trial. A simple method has been used for randomization. The randomization unit is Individual. Excel software has been used for randomization. Using unique codes as ID numbers, using random numbers generated by the software, participants were randomly assigned to the same volume in the intervention and placebo groups. (Description of randomization by Excel software: In the first step, we generated 50 random numbers according to the sample size, in the next step, we obtained the rank of these numbers obtained in the first step, and in the third step, we divided these numbers by 25, in the fourth step, the numbers that fell between zero and one were in the intervention group and the rest in the placebo group) The primary service method was used for allocation concealment, and someone outside our study performed allocation concealment and labeling of supplements.

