Food addiction will be diagnosed using a Modified Yale Food Addiction Scale Version 2.0 questionnaire. In this questionnaire, 12 criteria are examined. Both the symptom count score and the clinical significance criterion are used. For the "diagnosis" scoring option, a participant can meet for mild, moderate, or severe food addiction. At the beginning of the study, in the middle of the study (sixth week), and at the end of the study (twelfth week), anthropometric measurements, body composition, and calculation of body mass index will be done for each person. A digital scale will measure weight with an accuracy of 0.1 kg, with minimal clothing and no shoes. Height, waist, and hip circumference will be measured with an inelastic meter with an accuracy of 0.5 cm. Waist circumference will be measured at a distance between the lowest rib and iliac bone and hip circumference at the highest hip protrusion. Body mass index and waist-to-hip ratio are obtained by calculation. Body fat mass and muscle mass will be measured by bioelectrical impedance analysis (BIA). The participants' physical activity level is assessed using the standard questionnaire of activities (metabolic equivalents task) (MET) at the start, the sixth week, and the end of the study. Eating behavior is assessed using the Three-Factor Eating Questionnaire (TFEQ-R18) at the beginning, sixth week, and end of the study. Three 24-h food recall (2 regular days of the week and one day off) will be taken from participants at the beginning, the sixth week, and end of the study, also, a 24-h recall once a week, with telephone calls with patients. To measure blood biochemical parameters, at the beginning and end of the study, after 12–14 h of night fasting, five cc of venous blood samples will be taken from the participants. Blood samples taken in tubes containing sodium citrate anticoagulants will be collected and centrifuged in the laboratory of the Shahid Beheshti Nutrition Faculty. Serums will be stored at -80 °C until the tests are performed. Serum levels of leptin, serotonin (LDN ELISA Kit, Germany), and oxytocin (Crystal Day ELISA Kit, Shanghai) will be measured by the ELISA method with the human kit with the intra-assay and inter-assay CV of < 10.8% (serotonin), < 12% (leptin), and < 6.8% (oxytocin) kits in the laboratory of the Nutrition Institute of Shahid Beheshti University of Medical Sciences.

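### Weight and the other outcomes measured at weeks 0, 6 and 12 fall under three between-group analyses, and the plan does not say which test, or which ANOVA term, decides

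*Protocol article*

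**What the plan says.** All references are to the protocol article.

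- **Sample size.** The trial is sized on weight: "calculated based on weight as a main dependent variable". The SDs are 2.8 and 2.9, the difference 2.5, and the result 20 per group; then "assuming a drop of 20%, 25 patients will be admitted to each group".
- **Study outcomes.** "The primary outcomes of this clinical trial are the changes in anthropometric indices", listed as weight, hip circumference, waist-to-hip ratio, fat mass and muscle mass, together with the food addiction score. Measurements are taken at the start, then "in the middle of the study (sixth week), and at the end of the study (twelfth week), anthropometric measurements, body composition". The eating questionnaire has the same three times; the hormones have two.
- **Statistical analysis.** Between groups, normally distributed quantitative variables get a t-test on means at the start and at the end. Then: "A repeated ANOVA test will be used for the variables measured three times during the study". Covariance analysis is added for quantitative confounders, which are named as physical activity and the baseline values of the biochemical markers.
- **Adherence.** Only data from participants above 90% adherence are to be analysed.

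**The concern.** For weight, three between-group analyses are prescribed and none is ranked. Repeated ANOVA itself yields two candidate terms: the group main effect, which averages over all three visits including baseline, and group-by-time. The primary outcomes are defined as changes, yet the t-test compares raw means at the end. The covariance analysis, as its covariates are listed, does not adjust weight for baseline weight.

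Two things are at stake. If the reported result may be taken from any of these tests, the false-positive rate for weight exceeds 5%. And the tests differ greatly in sensitivity, so whether the trial finds an effect of the size it was planned for depends largely on which p-value is read. A smaller matter is that standard repeated ANOVA uses only participants with every visit, so week-6 values of later dropouts go unused.

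**Working it through.** **Plan's own figure.** Pooled variance = (2.8² + 2.9²)/2 = 8.125, so the pooled SD is 2.85. (The article labels 8.125 as Sp. It is the variance; this is a separate labelling slip.) n = 2 × 8.125 × (1.96 + 0.84)²/2.5² = 20.4 per group, against 20 stated. 20/0.8 = 25 enrolled, as stated.

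**Assumptions.** The article does not say whether 2.8 and 2.9 are SDs of change or of final weight; change is assumed. Baseline SD is not given; 10, 15 and 20 kg are used, with 3 kg as a low extreme. Changes over weeks 0–6 and 6–12 are independent with equal variance, and half the effect is present at week 6. There are 20 per arm, allocated equally.

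**Power, raw end-of-study t-test.** SD at week 12 = √(baseline SD² + 8.125); noncentrality = 2.5/(SD × √(2/20)).
- Baseline SD 10: SD 10.40, noncentrality 0.760, power 0.115
- Baseline SD 15: SD 15.27, noncentrality 0.518, power 0.080
- Baseline SD 20: SD 20.20, noncentrality 0.391, power 0.067

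**Power, ANOVA group term.** This is a t-test on the three-visit mean. The mean difference is (0 + 1.25 + 2.5)/3 = 1.25. The variance is baseline SD² + 8.125 × 5/18 = baseline SD² + 2.26. Power is 0.067, 0.058 and 0.054 for baseline SD 10, 15 and 20.

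**Power, tests that use change from baseline.** By simulation, group-by-time with the Greenhouse-Geisser correction and ANCOVA adjusted for baseline weight both give about 0.75 to 0.76, whatever the baseline SD. For comparison, a t-test on change has power 0.77.

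**Type I error (simulation, no true effect).** Each test alone is near 0.05. Uncorrected for sphericity, group-by-time is about 0.06.

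| Baseline SD | Any of end t-test, group-by-time (corrected), baseline-adjusted ANCOVA | Adding the group term |
|---|---|---|
| 3 kg | about 9% | about 11% |
| 10–20 kg | about 10–11% | about 11% |

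Three independent tests would give 1 − 0.95³ = 14.3%. The figures are lower because the tests are correlated.

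**Missing visits.** If each post-baseline visit is missed independently with probability 10% or 20% (assumed), complete cases out of 25 are 25 × 0.9² = 20.3 or 25 × 0.8² = 16.0. Participants with any post-baseline value number 25 × (1 − 0.1²) = 24.8 or 25 × (1 − 0.2²) = 24.0.

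If instead 20% simply leave after week 6, repeated ANOVA loses no one whom the end-of-study t-test would keep. With a week-6/week-12 change correlation of about 0.71 (r² = 0.5), using the week-6 data takes the variance factor from 1/20 = 0.050 to 0.5/20 + 0.5/25 = 0.045. The standard error falls from √(2 × 8.125 × 0.050) = 0.901 to √(2 × 8.125 × 0.045) = 0.855. Normal-approximation power rises from about 0.79 to 0.83.

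**The case against.** **Scope.** This is a condensed article. Naming the deciding test, the model term and the missing-data method is often left to an analysis plan, which is not shown. That excuses silence on missing visits. It does not fully excuse the Statistical analysis section, which is not silent: it commits the same outcomes to overlapping tests without an order.

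**Another reading.** The section could mean t-tests for variables measured twice, repeated ANOVA for those measured three times, and covariance analysis for adjustment. That is possible, but the t-test sentence carries no such restriction.

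**Which ANCOVA.** The simulated one adjusts for baseline weight, which the article's covariate list does not include. This is fair: the error figure describes a charitable version of the plan.

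Three stronger readings are tempting, and the document does not support them.

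- *Repeated ANOVA cannot detect the effect.* The 5 to 7% belongs to the group term alone, which the article never makes the treatment test. Since the primary outcomes are changes, group-by-time is the natural term, and it does about as well as ANCOVA.
- *Using baseline as an occasion inflates error.* It only dilutes the group term. Group-by-time stays valid with a sphericity correction. The inflation comes from the free choice among tests.
- *The method loses 20% of participants.* That is planned attrition, already covered by enrolling 25 per arm, and the 90% adherence rule may account for part of it. Dropping incomplete cases is how standard repeated ANOVA works, not something the article states. The extra loss is confined to those who miss week 6 but attend week 12.

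**Conclusion.** The point holds as a missing hierarchy among tests that are not interchangeable. For weight, taking any of the three between-group tests gives about 10 to 11% type I error at an assumed baseline SD of 10 to 20 kg, and about 9% at 3 kg. Planned-effect power at 20 per arm runs from about 7 to 12% (raw end t-test) to about 75 to 76% (group-by-time or baseline-adjusted ANCOVA).

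These figures rest on reading the sample-size SDs as SDs of change and on baseline SDs that the article does not give. With a baseline SD of 3 kg the gap narrows: the same formulas give 0.46 for the end t-test and 0.21 for the group term. The gain from keeping the week-6 data of dropouts is modest.

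The same overlap affects the other outcomes measured three times. Whether it reaches the food addiction score is unclear, because no follow-up times are given for it. This is worth correcting before unblinding.

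**What to change.** 1. For outcomes measured three times, replace the end-of-study t-test and repeated ANOVA as the between-group test with one linear mixed model (SPSS MIXED). Outcomes: weeks 6 and 12. Fixed effects: arm, visit, arm-by-visit and the outcome's own baseline value. Covariance: unstructured. Population: all randomised participants with any post-baseline value.
2. State that the week-12 arm contrast with its 95% CI is the deciding test for each such outcome, with weight, the sizing variable, as the lead outcome.
3. For the hormones, measured twice, use ANCOVA on the baseline value.
4. Reconcile the Adherence sentence that limits analysis to participants above 90% adherence with this population, for example by keeping it as a per-protocol sensitivity analysis. The exclusion criteria also remove such participants from the study. If that ends their measurements, the model can use only what was recorded before.

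Cost: slightly more programming in the named software and a changed analysis set. The model itself needs only measurements already scheduled. It gives one test per outcome, not one for the trial; multiplicity across the six primary outcomes is a separate matter that this change does not settle.

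### The covariance analysis names physical activity as a confounder without limiting it to week 0, so the rule as written permits adjustment for activity measured after randomisation

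*Protocol article*

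**What the plan says.** In the protocol article, Statistical analysis gives both the method and the covariates. The method: "Covariance analysis will be used to eliminate the effect of quantitative confounding factors". The covariates: "Quantitative confounding factors are physical activity and baseline values of the biochemical markers". In that second sentence, the restriction to baseline is attached to the biochemical markers and not to physical activity.

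Study outcomes describes how activity is measured: "physical activity level is assessed using the standard questionnaire", scored as "metabolic equivalents task) (MET) at the start, the sixth week, and the end of the study". Two of the three available activity values are therefore obtained after treatment has started.

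Randomization describes an individually randomised trial with equal arms: "participants were randomly assigned to the same volume in the intervention and placebo groups". Weight is one of the primary measures ("The primary outcomes of this clinical trial are the changes in anthropometric indices") and is the variable on which the sample size is based.

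**The concern.** Randomisation makes the arms comparable, apart from chance, on everything fixed before allocation. A pre-randomisation covariate can go into a covariance analysis safely and may improve precision. A variable measured at week 6 or week 12 is different. It cannot have influenced allocation, so it does not confound the comparison, but treatment may have influenced it. Here later activity could change because of the probiotic or because a patient has lost weight.

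If such a value is the covariate, the adjusted difference no longer estimates the effect of being assigned probiotic. The part of the effect that acts through activity, or that shows up in activity, is removed. If treatment shifts activity, and activity and weight also share other causes, the adjustment can produce a difference where the true effect is zero.

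There is also a matter of analytic freedom. With three activity values and no rule, the choice could be made after the data are seen, in a trial planned around 20 analysable patients per arm.

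**Working it through.** **1. What the text fixes and leaves open**

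| Covariate | Times measured | Time point named for the covariance analysis |
|---|---|---|
| Biochemical markers | start, week 12 | baseline |
| Physical activity | start, week 6, week 12 | none |

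No other section restricts activity to the week-0 value.

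**2. The plan's own sample size, to fix the scale**

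Inputs from Sample size: S1 = 2.8, S2 = 2.9, difference 2.5 (no unit printed; taken as kg), two-sided α = 0.05, power 80%.

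- Pooled variance = (2.8² + 2.9²)/2 = 8.125, so pooled SD = √8.125 = 2.85. The article prints 8.125 as Sp; it is a variance and is used as such here.
- n = 2 × 8.125 × (1.960 + 0.842)² / 2.5² = 20.4 per arm. The stated 20 is reproduced to within rounding.
- 20/(1 − 0.20) = 25 per arm, as stated.

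The point disputes none of these figures.

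**3. Illustration A: treatment shifts week-12 activity**

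The article gives no data on activity, so both inputs below are assumptions:

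- a = treatment shift in week-12 activity, in within-arm SD units;
- r = within-arm correlation of that activity with weight change, giving a slope b = r × 2.85 kg per SD.

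Adjusted difference = 2.5 − a × b, with the shift acting in the direction of the benefit.

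| a | r = 0.2 (b = 0.57) | r = 0.4 (b = 1.14) | Share removed |
|---|---|---|---|
| 0 | 2.50 | 2.50 | 0% |
| 0.2 | 2.39 | 2.27 | 5 to 9% |
| 0.4 | 2.27 | 2.04 | 9 to 18% |
| 0.6 | 2.16 | 1.82 | 14 to 27% |

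Example: a = 0.4, r = 0.4 gives 2.5 − 0.4 × 1.14 = 2.04. A simulation of 1,000,000 subjects at these values also gave 2.04 when adjusting for week-12 activity, and 2.50 when adjusting for a baseline covariate.

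Power at 20 per arm (normal approximation, residual SD = 2.85 × √(1 − r²)) is 79% for the unadjusted comparison. For the adjusted comparison it is 73% and 70% at a = 0.4, and 69% and 59% at a = 0.6, for r = 0.2 and 0.4 respectively. With a = 0, adjustment raises power, to 81% and 86%.

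The same formula covers the spurious difference. If the true effect is zero but treatment shifts activity by a = 0.4, the adjusted difference is 0 − 0.4 × 0.57 = −0.23 to 0 − 0.4 × 1.14 = −0.46 kg.

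**4. Illustration B: weight loss drives activity**

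The probiotic need not act on activity. If week-12 activity simply follows weight change with within-arm correlation r, then a = r × 2.5/2.85. The bias is a × b = r × (2.5/2.85) × r × 2.85 = 2.5 × r², and the adjusted difference is 2.5 × (1 − r²):

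- r = 0.2: 2.5 × 0.96 = 2.40
- r = 0.3: 2.5 × 0.91 = 2.28
- r = 0.4: 2.5 × 0.84 = 2.10

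**5. After the fix**

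With week-0 activity as the covariate the target stays at 2.5, and the planned 20 (25) per arm is unchanged.

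**The case against.** The strongest reply is that this is an omission and not a decision. A reader might infer that the trial plans to adjust for week-6 or week-12 activity. The article does not say so. The contrast in wording has an ordinary explanation: the serum markers are themselves outcomes, so the word baseline is needed to separate covariate from outcome, whereas activity is not an outcome. Repeated activity measurement may serve only monitoring, and a condensed article may leave covariate timing to a fuller document. This stands to the extent that the point concerns what the rule permits. It does not dispose of the point: the article chose to name its covariates, gave a time for one, and left the other open to two values that should not be used.

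A reader might also infer that the trial's whole treatment comparison is at risk. It is not. The same section plans between-group t-tests at the end of the study and repeated-measures ANOVA for variables measured three times. Those comparisons carry no activity adjustment. Only the covariance analysis is affected, and only if a later value is used.

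On mechanism, the article's rationale runs through the microbiome, hormones and eating behaviour. It proposes no effect of the probiotic on activity, and both arms receive the same diet and cognitive behavioural therapy under blinding. A large direct shift is therefore not something the document supports, and the upper rows of illustration A should be read accordingly. Illustration B needs no direct effect, so the risk remains.

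Finally, the section plans between-group tests at the start of the study, and a reader might infer that these select the covariates. The article does not state this. It names its quantitative covariates in advance.

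**Conclusion.** The point holds as a badly fixed covariate definition. The text permits a post-randomisation value of physical activity in the covariance analysis, and nothing in the article excludes it. The document does not show that such a value will be used, nor that any result will be biased.

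The size cannot be derived from the document. If activity responds to neither treatment nor weight, there is no bias. On the assumed ranges, the adjusted weight difference falls from 2.5 to between 2.39 and 1.82 when treatment shifts activity by 0.2 to 0.6 SD, and to between 2.40 and 2.10 when weight loss drives activity. These figures assume linear relations, a shared SD of 2.85 and correlations of 0.2 to 0.4. With a shift in the opposite direction, the adjusted difference would be inflated instead. The point is worth correcting because it bears on a primary outcome and costs almost nothing to settle.

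**What to change.** Replace the covariate sentence in Statistical analysis with: *Quantitative covariates are baseline (week-0) physical activity and the baseline value of the outcome being analysed.* Add that week-6 and week-12 activity will be reported descriptively by arm.

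Naming the baseline value of each outcome extends to weight and the other outcomes what the article now provides only for the biochemical markers. The planned regression adjustment for qualitative factors stays as it is.

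The cost is one or two sentences. Activity and all outcomes are already scheduled to be measured at the start, so no visit, measurement or patient is added. The article describes the trial as still enrolling; the change should be recorded before unblinded data are analysed.
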